### Clinical assessment and questionnaires

The primary outcome included EC50 (concentration-response parameter: concentration which produces 50% of the maximal effect) for IL-1β release, to determine the responsiveness of PBMC and SFMC to LPS and PAM3 stimulation. Osteoarthritis severity of the painful knee will be graded by an orthopaedic surgeon based on Kellgren-Lawrence and self-assessed pain scores will be determined by the patient preoperatively for both knees using the NRS-pain scores. Additionally, preoperative mental state will be assessed by completing two Patient Reported Outcome Measures (PROM): the Hospital Anxiety and Depression Scale (HADS) questionnaire,^34^ and the Pain Catastrophizing Scale (PCS) questionnaire.^35 36^ The HADS consists of an anxiety (HADS-A) and a depression (HADS-D) subscale, each including seven items scoring 0–3, resulting in a total maximum score of 21 per subscale. Scores of 8–11 are considered borderline anxiety or depression, whereas scores>11 are considered presumable anxiety or depression.^37^ In this study, an HADS-A or HADS-D score ≥8 will be categorised as the presence of anxiety or depression, respectively.^34 38^ The PCS is a validated questionnaire consisting of 13 statements regarding feelings and thoughts during experiencing pain.^35 36^ Patients rate these statements on a 5-point Likert scale ranging from ‘not at all’ to ‘all the time’ with the total score ranging from 0 (no catastrophising) to 52 (severe catastrophising). A score of 30 or higher is considered clinically relevant catastrophising;^36 39^ as such, patients will be considered pain catastrophizing (PC) or non-PC patients.

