### Sample size calculation

A sample size calculation based on achieving 90% power and a Type 1 error rate of 5% was chosen. The calculation was based on primary analyses and determined that 24 participants in total (12 participants per group) would be required to detect a 2.40 difference in the Least Squares means for EC50 (concentration-response parameter: concentration which produces 50% of the maximal effect, to determine the responsiveness of PBMC and SFMC to LPS and PAM3 stimulation) assuming a within-group SD of 1.78. The clinically significant difference in EC50 was estimated based on parameters described by Evans *et al*.^29^ To account for a potential 10% loss to follow-up and safety margin with regards to sample analyses, a total sample of 40 participants (20 per group) is to be recruited.

It should be noted that the calculated sample size was based on the primary analysis and may not provide sufficient statistical power for all planned secondary analyses, such as investigating associations between immune responsiveness (PBMCs and SFMCs responses) and psychological symptoms including anxiety, depression or pain catastrophising. General statistical guidance for multivariable modelling recommends an adequate number of observations per covariate to ensure model stability (eg, 10 patients per use of 1 covariate). Therefore, the number of covariates included in secondary analyses will be kept limited (only one psychological variable per model) to maintain analytical feasibility. As these secondary analyses are exploratory in nature, their findings will be interpreted accordingly. The present study represents an initial exploratory investigation of neuroimmune pain biomarkers within an orthopaedic population.

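### The article defines HADS-A, HADS-D and PCS only as yes/no categories; if these enter the secondary models, about a quarter to a half of the power at n=20 is lost

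*Protocol article*

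**What the plan says.** The section Clinical assessment and questionnaires describes HADS-A and HADS-D as subscales with a maximum of 21 and PCS as a 0 to 52 score. It then sets a rule for this study: "In this study, an HADS-A or HADS-D score ≥8 will be categorised as the presence of anxiety or depression, respectively". For PCS, "A score of 30 or higher is considered clinically relevant catastrophising", and on that basis "patients will be considered pain catastrophizing (PC) or non-PC patients". These are the only working definitions of the psychological variables in the article.

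The second secondary aim is to relate immune responses to anxiety, depression and pain catastrophising. The Sample size calculation section limits each secondary model to one psychological variable and concedes that the sample "may not provide sufficient statistical power for all planned secondary analyses". The Data analysis plan calls all secondary analyses exploratory. Neither section says whether the score or the category goes into the model.

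**The concern.** Dichotomising an ordered score discards information that has already been collected. A patient scoring 7 on a HADS subscale is treated as different in kind from one scoring 8, while a patient scoring 8 is treated as identical to one scoring 20. The cut at 8 also merges the two upper HADS bands that the article itself distinguishes (borderline and presumable).

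Nothing is gained in return. A continuous score uses one degree of freedom, as a yes/no variable does, so the rule of one psychological variable per model gives no reason to cut. With 20 patients the result of a dichotomised analysis may rest on a small group on one side of the threshold. A real association is then more easily missed, and an apparent one depends more on a few individuals.

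**Working it through.** **The plan's own figure.** The only power calculation concerns the primary comparison. Inputs from the Sample size calculation section: 90% power and 5% type 1 error (two-sided assumed; the article does not say), a difference of 2.40 in EC50, and an SD of 1.78. By the normal approximation, n per group = 2 × (1.960 + 1.282)² × (1.78 / 2.40)² = 2 × 10.51 × 0.550 = 11.56, rounded up to 12. This agrees with the stated "24 participants in total (12 participants per group". The article gives no power figure for the psychological analyses, so there is none to reproduce.

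**Inputs for the check.**
- n = 20 (patients only) and n = 40 (patients plus healthy controls, possible for blood only), from Participants and eligibility criteria.
- True correlation between score and IL-1β parameter: 0.4, 0.5 and 0.6. Assumed.
- Share above the cut: 50%, 30% and 20%. Assumed.

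**Large-sample loss.** For a normally distributed score cut so that a share p lies above the threshold z, the correlation shrinks by the factor f = φ(z) / √(p(1 − p)), and the efficiency relative to the continuous score is f².
- p = 50%: f = 0.399 / 0.500 = 0.798, f² = 0.64
- p = 30%: f = 0.348 / 0.458 = 0.759, f² = 0.58
- p = 20%: f = 0.280 / 0.400 = 0.700, f² = 0.49

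Cutting with 20% above the threshold is therefore roughly equivalent to discarding half of the patients.

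**Power at the actual sample sizes.** Simulation of bivariate normal data, 400,000 data sets for each combination of n and correlation, two-sided 5% level. The Pearson test on the score is compared with the pooled t-test on the same score after the cut.

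| n | Correlation | Continuous | 50% above | 30% above | 20% above |
|---|---|---|---|---|---|
| 20 | 0.4 | 43% | 28% | 26% | 22% |
| 20 | 0.5 | 64% | 43% | 39% | 33% |
| 20 | 0.6 | 84% | 61% | 55% | 47% |
| 40 | 0.4 | 74% | 54% | 49% | 42% |
| 40 | 0.5 | 92% | 76% | 70% | 62% |
| 40 | 0.6 | 99% | 91% | 87% | 79% |

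**Relative loss.** From the unrounded results, the share of power lost at n = 20 runs from 27% (correlation 0.6, half above the cut) to 49% (correlation 0.4, 20% above). At n = 40 it runs from 8% to 43% over the same grid.

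**Group sizes among 20 patients.** The expected number above the cut is 10, 6 and 4 at 50%, 30% and 20%. If only 10% were above it, the expected number would be 2. The chance of having fewer than two such patients would be 0.9²⁰ + 20 × 0.1 × 0.9¹⁹ = 0.122 + 0.270 = 39%.

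**The case against.** The strongest reply is that the cut-offs stand in the section on measures, where they define clinical labels. The Data analysis plan speaks of associations with patient-reported measures, and the form in which they enter a model is commonly left to an analysis plan that is not shown. This stands in part: the article never says that the categories replace the scores in the models, so the loss is conditional. It does not remove the point. The rule is worded for this study, is the only definition given, and is nowhere limited to description.

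Four stronger readings are tempting, and the article does not support them.
- *Power is nearly halved.* That needs about 20% above the cut as well as n = 20. With half of the patients above it, the loss is about a quarter to a third.
- *Only a handful of patients will be positive.* The exclusion criteria do not remove anxiety, depression or catastrophising, and the Introduction links pain before TKA to psychological symptoms. A low share cannot be presumed from the requirement of good general health.
- *The plan itself calls these analyses underpowered.* It says only that the sample "may not provide sufficient statistical power for all planned secondary analyses".
- *The aim becomes unanswerable.* Some power remains after the cut, and at a correlation of 0.4 the continuous score reaches only 43% with 20 patients. The fix improves the analysis but does not rescue it.

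It is also fair to say that 20 is not the only possible sample. The abstract has all participants completing the psychological questionnaires, so blood analyses could use 40 people, with a smaller loss. Such pooling would mix the psychological score with patient or control status, and synovial fluid analyses cannot exceed 20 patients.

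**Conclusion.** The point holds in conditional form. The article fixes yes/no categories for three ordered scores and does not say that the scores are kept continuous. If the categories are used for the secondary aim, power at n = 20 falls by about one quarter to one half, given correlations of 0.4 to 0.6 and 20% to 50% of patients above the cut. With all 40 participants pooled the loss is smaller. Correlation, share above the cut and normality are assumptions, so the range should be read and no single figure taken from it.

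Exploratory status lowers the stakes but does not justify discarding collected information. The point concerns a secondary aim only and does not touch the primary comparison or the recruitment target.

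**What to change.** Add one sentence to the Data analysis plan: HADS-A, HADS-D and PCS enter the secondary models as continuous scores, one per model (or are related to the IL-1β parameters by Spearman correlation), and the cut-offs of 8 and 30 serve only to describe the sample.

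The cost is that sentence. The scores are collected in any case, no further participants or samples are needed, and the article states that recruitment had not begun, so the change can be made before any data exist.

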### Sample collection

Preoperatively, at the pre-admission clinic 2–4 weeks before surgery, enrolled TKA-awaiting patients (n=20) will receive routine venous blood sampling for elective surgery preparations at Noarlunga Hospital. At that same blood collection moment, a total of 30 mL of blood will be collected for this study: 10 mL for the functional immune stimulation assay used to quantify cytokine release (IL-1β) (ie, ‘painCELL test’), 10 mL for the HS imaging-based analysis of immune cells used to characterise cellular autofluorescence signatures and identify potential phenotypic differences between participant groups (ie, ‘painHS test’) and 10 mL for storage and backup in case of experimental assay complications. Also, all preoperative questionnaires (HADS, PCS and NRS-pain) will be completed during this visit.

Subsequently, perioperatively during the elective TKA surgery, synovial fluid will be collected from the painful knee receiving TKA surgery, just after opening the knee joint. A total of 30 mL of synovial fluid will be collected for this study: 10 mL for the painCELL test, 10 mL for the painHS test and 10 mL for storage and backup in case of experimental assay complications.

Similarly, the contralateral pain-free knee will be punctured for 5–30 mL synovial fluid directly after surgery when the patient is still under narcosis, so that the patient will experience no additional discomfort. This procedure is included to enable within-subject comparison between painful osteoarthritic and pain-free joints within the same patient, thereby reducing inter-individual variability in immune response measurements. The aspiration will be performed under sterile operating theatre conditions by an experienced orthopaedic surgeon, following standard aseptic procedures to minimise the risk of complications such as infection.

All healthy blood-control individuals without pain symptoms in both knees (n=20) will attend Flinders Medical Centre or Noarlunga Hospital, where similarly venous blood samples will be collected for the study, which includes 30 mL of blood in total: 10 mL for the painCELL test, 10 mL for the painHS test and 10 mL for storage and backup in case of experimental assay complications.

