**Methods and analysis:**

This is a protocol for a prospective cross-sectional matched-subject observational study. We will include 20 adults undergoing unilateral primary TKA for painful advanced knee osteoarthritis, their contralateral pain-free knees as internal controls and 20 age and sex matched healthy controls without joint pain or functional limitation. All participants will undergo standardised clinical assessment and complete pain and psychological PROMs. In patients with TKA, venous blood will be collected pre-operatively. During TKA surgery, synovial fluid will be aspirated from the painful operated knee and the contralateral pain-free knee. Healthy controls will provide a single venous blood sample at a hospital visit. Peripheral blood mononuclear cells and synovial fluid mononuclear cells will be stimulated ex vivo with toll-like receptor 2 and 4 agonists to quantify IL-1β release. In parallel, hyperspectral imaging will characterise unstimulated immune cell phenotypes. Multivariable statistical and machine-learning approaches will relate biomarker profiles to pain and psychological PROMs.

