### Laboratory procedures

#### PainCELL sample analysis

Venous blood collected in EDTA-coated vacutainer tubes and the synovial fluid collected in sodium citrate-coated tubes/sterile containers for the painCELL test will immediately be inverted several times to prevent blood from clotting. For the PBMC and SFMC isolation success to be maximised, the blood and synovial fluid will be cooled to room temperature before the cell isolation procedures initiate (30–60 min, depending on the ambient temperature). PBMCs are isolated using Optiprep density medium (Sigma-Aldrich #D1556; Castle Hill, NSW, Australia) as directed by the manufacturer using the mixer flotation method, as previously described.^23 26 27^ Due to the expected considerably small amount of synovial fluid available from sampling, this last step using Optiprep will not be performed for the SFMCs.

Isolated PBMCs and all SFMCs are diluted to 10^6^ cells/mL in enriched Roswell Park Memorial Institute Medium (RPMI) 1640 (10% fetal bovine serum, 2 mM l-glutamine and 1% penicillin/streptomycin) and plated into 96 well plates (100 µL per well). Various concentrations of innate immune stimulants will be added into the wells which include a TLR-2 agonist (Pam3; Merck #506350; Darmstadt, Germany; from 12.5 pg/mL to 1 mg/mL), and a TLR-4 agonist (LPS; InvivoGen #TLRL-3PELPS; San Diego, California, USA; from 12.5 pg/mL to 10 mg/mL) in a final volume of 200 mL/well. Plates are then incubated for 24 hours, following which 150 mL of the supernatant will be removed, transferred to a separate 96 well plate and stored at −80°C for later analysis. Supernatants are analysed using a Human Interleukin 1 eta (IL-1β) OptEIA ELISA Set II (BD Biosciences #557953; San Jose, California, USA) per the manufacturer’s instructions. The standard curve range for this assay is estimated to be 3.9–500 pg/mL. Supernatants are added to the ELISA either neat or diluted 1:10 to ensure the quantified values fall within the limits of the standard curve.

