### Data analysis plan

Primary analyses aim to assess whether peripheral immune response parameters differ between painful osteoarthritic knees and pain-free controls. This will be evaluated using both within-subject comparisons (painful knee vs contralateral pain-free knee in patients undergoing TKA for synovial fluid analyses) and between-group comparisons (patients vs healthy controls for peripheral blood analyses). Secondary analyses will explore associations between immune response parameters and PROMs for pain intensity and psychological factors including anxiety, depression and pain catastrophising. All secondary analyses, including multivariable and machine-learning approaches, are exploratory in nature and aimed at hypothesis generation rather than confirmatory inference.

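### In the synovial-fluid comparison, pain status is fully confounded with sampling time and access: painful knees are sampled early through the opened joint, control knees by puncture after surgery

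*Protocol article*

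**What the plan says.** The Sample collection section describes the two synovial collections separately.

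- Painful knee: "synovial fluid will be collected from the painful knee receiving TKA surgery, just after opening the knee joint". The planned volume is fixed: "A total of 30 mL of synovial fluid will be collected for this study".
- Pain-free knee: "the contralateral pain-free knee will be punctured for 5–30 mL synovial fluid directly after surgery when the patient is still under narcosis".

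The purpose of the second collection is stated there: "This procedure is included to enable within-subject comparison between painful osteoarthritic and pain-free joints within the same patient". The Data analysis plan makes this one of the two primary comparisons ("painful knee vs contralateral pain-free knee in patients undergoing TKA for synovial fluid analyses"); the other is blood from patients against blood from healthy controls. The strengths and limitations box says that using the contralateral knee as internal control strengthens causal inference. Its limitations do not mention that the two knees are sampled differently.

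The abstract describes the sampling as one event: "During TKA surgery, synovial fluid will be aspirated from the painful operated knee and the contralateral pain-free knee". That does not agree with a puncture after surgery.

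For the assay, the PainCELL sample analysis section omits density separation for synovial cells: "this last step using Optiprep will not be performed for the SFMCs".

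**The concern.** A within-patient comparison removes what the two knees share. It does not remove a difference in how they are sampled if that difference runs the same way in every patient. Here no painful knee is sampled late or by puncture, and no pain-free knee is sampled early or through an open joint.

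The readout is innate immune responsiveness, and two mechanisms by which the sampling could affect it are plausible.

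- The control sample follows a longer surgical and anaesthetic exposure than the painful sample. The protocol itself treats recent major surgery, trauma and immune-active medication as reasons for exclusion.
- The amount of blood mixed into the fluid may differ between an opened joint and a puncture. Synovial cells are plated without density separation, and blood mononuclear cells are stimulated with the same agonists for the same IL-1β readout, so admixed blood cells could contribute to the measured response.

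At stake is what the synovial contrast can be said to show. A difference between knees could reflect pain, sampling or both, and a true pain difference could be masked.

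**Working it through.** **1. The plan's own figure.** The Sample size calculation section gives a difference of 2.40, SD 1.78, 5% type 1 error and 90% power. Two-sided, for two independent groups:

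n per group = 2 × [1.78 × (1.960 + 1.282) / 2.40]² = 11.56, rounded up to 12, or 24 in total.

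The stated figure reproduces under the normal approximation. The noncentral t version gives 13 per group, with 88.4% power at 12. The point made here does not depend on this figure.

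**2. The two collections side by side**

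| | Painful knee | Pain-free knee |
|---|---|---|
| Time | during surgery, just after the joint is opened | directly after surgery |
| Access | opened joint | puncture |
| Anaesthesia | under way | still under way |
| Volume | 30 mL | 5–30 mL |

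**3. Can any model separate pain from sampling?** For patient i and knee j, write

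Y = patient effect + β·pain + γ·late + δ·puncture + error.

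In every patient the painful knee has pain = 1, late = 0, puncture = 0, and the control knee has pain = 0, late = 1, puncture = 1. The paired difference, painful minus control, therefore has mean β − γ − δ. Only this sum can be estimated.

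In design-matrix terms, 20 patient effects plus pain give rank 21. Adding the columns for time and access makes 23 columns, and the rank stays 21. No covariate adjustment, paired model or classifier can recover β alone.

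**4. What a procedural shift could do (illustration).** The documents give neither the size of any shift nor the within-patient correlation ρ, so both are assumed. Take 20 pairs, SD 1.78, no pain effect and a two-sided 5% paired t-test. The SD of the paired difference is 1.78 × √[2(1 − ρ)], which is 2.52 at ρ = 0 and 1.38 at ρ = 0.7. The noncentrality is shift / (SD of difference / √20). For a shift of 0.6 this is 1.07 at ρ = 0 and 1.95 at ρ = 0.7.

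Share of studies declared significant:

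| ρ | no shift | shift 0.6 (¼ of 2.40) | shift 1.2 (½ of 2.40) |
|---|---|---|---|
| 0 | 5% | 17.3% | 52.5% |
| 0.3 | 5% | 22.7% | 67.6% |
| 0.5 | 5% | 29.9% | 81.6% |
| 0.7 | 5% | 45.5% | 95.8% |

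These are not error rates of the planned analysis, which is an F-test on fitted curve parameters (Primary outcome analysis: painCELL data). They show only that a shift well below the planned effect would matter with this number of pairs.

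**5. Scope.** The same synovial samples form two of the four sample groups in Secondary outcome analysis: painHS data, so the confounding carries over there. Blood in patients is taken at the pre-admission visit and blood in controls at a hospital visit, so neither blood sample is touched by it.

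**The case against.** The study is declared exploratory and hypothesis-generating, one of its two primary comparisons is unaffected, and the laboratory is blinded. The first two points stand: they limit the damage to the synovial contrast, and the study as a whole is not invalidated. Blinding does not help, because the difference arises at collection. The exploratory label does not help either, since a hypothesis about pain drawn from this contrast would carry the same ambiguity.

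Several stronger readings are tempting, and the documents do not support them.

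- A reader might infer that the painful sample is free of surgical and drug exposure. It is taken during surgery, after the joint has been opened, and both samples are taken under anaesthesia. The two differ in amount and duration of exposure.
- A reader might infer that the painful sample is contaminated with blood and the control sample is clean. The documents do not say so. A puncture can also draw blood, and density separation is omitted for both knees.
- A reader might infer that the collecting device differs. The abstract speaks of aspiration from both knees, and the device for the painful knee is not stated. What does differ in every pair is access and timing.
- A reader might infer that matching the collections needs nothing new because both are already planned. Only the control knee is described as punctured, so aligning the two would change at least one of them and the theatre workflow.

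**Conclusion.** The point holds for the synovial comparison and for the two synovial imaging groups. Pain status is completely confounded with sampling time and access, and a later analysis plan cannot undo that. This conclusion rests only on the collection sequence in the Sample collection section being applied as written in all 20 patients.

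The size and direction of any bias cannot be derived from the documents. Surgical and anaesthetic exposure and blood admixture are plausible mechanisms, not documented effects, and the percentages above rest on assumed shifts and correlations. A bias of any particular size is therefore not shown. What is shown is that the causal-inference claim in the strengths and limitations box is not supported for this contrast, and that the abstract and the Sample collection section disagree on when the control knee is sampled.

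**What to change.** 1. Reconcile the abstract with the Sample collection section on the timing of the control-knee collection.
2. Ask the surgical team and the ethics committee to decide whether both research samples can be taken at the same point under anaesthesia and by the same access. Feasibility is their decision. The reason the protocol gives for the present timing of the puncture is that the anaesthetised patient has no added discomfort.
3. In either case, record the sampling time and visible blood staining for each knee, and add a sensitivity analysis that leaves out blood-stained samples. This addresses blood admixture only; it does not resolve the timing difference.
4. If sampling cannot be matched, remove the causal-inference claim for this contrast, list the sampling difference as a limitation, and report the result as pain status combined with sampling time and access. Apply the same wording to the synovial imaging groups.

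The cost is a small change to theatre workflow if matching is agreed, two extra recorded items per knee, and a protocol amendment. Ethics and dissemination states that recruitment and sample collection had not begun, so this is the cheapest time to make the change.

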## Methods and analysis

### Aim, design and setting of the study

This study concerns an exploratory cross-sectional matched-subjects observational study and will be performed in accordance with the Declaration of Helsinki guidelines, and reported in accordance with Strengthening the Reporting of Observational Studies in Epidemiology (STROBE) guidelines. All aspects of this study have been approved by the Southern Adelaide Clinical Human Research Ethics Committee (SAC HREC), Southern Adelaide Local Health Network (SALHN) (2024/HRE00253). Trial registration at the Australian and New Zealand Clinical Trials Registry was completed before commencement of participant recruitment and enrolment (Trial Registration Number: ACTRN12626000084381, date: 22–01-2026. Universal Trial Number: U1111-1332-7067).

Recruitment is planned to commence in March 2026 and is expected to continue for approximately 6 months. Laboratory analyses will be performed in batches during and after recruitment. The investigators performing the laboratory analyses are blinded to the clinical status of the patients. Participant enrolment, clinical assessments, and sample collection will be conducted in Noarlunga Hospital (Flinders Medical Centre), Adelaide. Investigators will not be blinded to group allocation (group with patients awaiting TKA or group with healthy controls). Sample analyses and data analyses will be performed in the Neuroimmunopharmacology Laboratory of Helen Mayo South Building, University of Adelaide.

The primary aim of this exploratory study is to assess whether peripheral immune response parameters (IL-1β release following TLR-2 and TLR-4 activation) differ between painful osteoarthritic knees and pain-free controls. This will be conducted through measuring peripheral immune responses (pain biomarkers, ie, IL-1β expression), quantified from both PBMCs and SFMCs following TLR-2 and TLR-4 activation using PAM3CSK4 (PAM3, a synthetic lipopeptide which functions as an agonist for TLR-2) and lipopolysaccharide (LPS, ie, endotoxin, gram-negative bacterial cell wall component which functions as an agonist for TLR-4), between patients with symptomatic knee osteoarthritis awaiting TKA and pain-free healthy controls.

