### Recruitment and enrolment procedures

Initial recruitment of 20 patients awaiting a unilateral primary TKA for symptomatic (painful) advanced osteoarthritis at Noarlunga Hospital—SALHN will be via knee arthroplasty surgeons at the orthopaedic department. The recruitment of the 20 healthy controls without knee symptoms in both knees will also be performed via knee arthroplasty surgeons at the orthopaedic department of Flinders Medical Centre and Noarlunga Hospital.

All of these patients will be approached by email, which will include links to the study information. An additional email will be sent to all interested patients willing to participate, including the informed consent form, and a more detailed overview of the study.

For all participants who complete informed consent, eligibility will be reviewed through the electronic health-record system according to the inclusion and exclusion criteria, and baseline patient demographics (age, gender, body mass index [BMI], smoking, American Society of Anesthesiologists (ASA) physiological status classification, side of painful and pain-free control knee and other comorbidities) and preoperative medication, specifically pain medication, will be collected. Subsequently all patients (n=40) will be contacted by phone to confirm the presence and absence of all inclusion criteria and exclusion criteria, respectively.

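### Patients' blood is drawn only at Noarlunga but controls' blood may be drawn at either of two hospitals, so collection site may differ by group in the primary blood comparison

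*Protocol article*

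**What the plan says.** All references are to the protocol article.

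- **Patients.** Under Sample collection, "enrolled TKA-awaiting patients (n=20) will receive routine venous blood sampling for elective surgery preparations at Noarlunga Hospital", at the pre-admission clinic 2–4 weeks before surgery. The study blood comes from that draw: "At that same blood collection moment, a total of 30 mL of blood will be collected for this study".
- **Controls.** The same section says that the 20 controls "will attend Flinders Medical Centre or Noarlunga Hospital, where similarly venous blood samples will be collected for the study". No split between the hospitals is given. Recruitment and enrolment procedures has them recruited through "knee arthroplasty surgeons at the orthopaedic department of Flinders Medical Centre and Noarlunga Hospital".
- **General statement of site.** Aim, design and setting of the study says: "Participant enrolment, clinical assessments, and sample collection will be conducted in Noarlunga Hospital (Flinders Medical Centre), Adelaide". It places all sample analyses in one University of Adelaide laboratory, whose staff are blinded to clinical status.
- **Matching.** Participants and eligibility criteria matches controls on age and sex. Hospital is not a matching factor.
- **Role in the analysis.** The Data analysis plan makes patients versus healthy controls in peripheral blood one of the two primary comparisons.
- **Before isolation.** PainCELL sample analysis says that "the blood and synovial fluid will be cooled to room temperature before the cell isolation procedures initiate (30–60 min, depending on the ambient temperature"). Cells are isolated, plated and stimulated first. Only the supernatant is then frozen.

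**The concern.** The permitted collection sites differ by group under a rule that the plan itself states: one hospital for patients, two for controls. No patient can be drawn at Flinders, while any number of controls from 0 to 20 can be.

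The painCELL test measures the response of freshly isolated cells, so what happens to the tube before isolation is part of the measurement. If site affects that handling, or the delay before isolation, the effect enters the patient–control contrast as an apparent disease effect. Laboratory blinding and a single laboratory protect the assay and its reading. They do not remove a difference that arises before the sample arrives.

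The synovial comparison is not touched, because both knees are sampled in the same patient. The blood comparison has no such internal control.

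The two statements of where samples are collected also do not clearly agree. One names Noarlunga with Flinders in brackets. The other offers controls a choice of two hospitals.

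**Working it through.** **1. The plan's own figure.** Inputs from Sample size calculation: difference 2.40 in EC50, SD 1.78, power 90%, type I error 5% (two-sided assumed, as the article does not say).

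n per group = 2 × (1.960 + 1.282)² × 1.78² / 2.40² = 11.56, so 12 per group and 24 in total. This reproduces the stated figure. The plan recruits 20 per group.

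**2. Bias from site.** Let f be the share of controls drawn at Flinders and s the site shift in SD units. Neither is in the article, so both are assumed. With no true group difference:

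- bias in the group difference = f × s × 1.78
- standard error with 20 per group = 1.78 × √(2/20) = 0.563
- standardised shift = f × s × √10

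The false-positive rate is the chance that a two-sided 5% test rejects. It is shown by normal approximation, and by simulation of the t-test, which allows for the extra spread among controls when two sites are mixed.

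| f | s (SD) | Bias (EC50 units) | Share of 2.40 | Normal approximation | Simulation |
|---|---|---|---|---|---|
| 0 | any | 0 | 0% | 5% | – |
| 0.5 | 0.25 | 0.22 | 9% | 6.8% | about 7% |
| 0.5 | 0.5 | 0.45 | 19% | 12.4% | about 11% |
| 0.5 | 1 | 0.89 | 37% | 35.3% | just over 29% |

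Example, third row: 0.5 × 0.5 × √10 = 0.79. The rejection probability is 1 − Φ(1.96 − 0.79) + Φ(−1.96 − 0.79), about 12%.

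**3. What the analysis can recover.** If some controls are drawn at Noarlunga, patients can be compared with those controls alone. With 20 patients and m such controls, power at the plan's effect and SD is Φ(2.40 / [1.78 × √(1/20 + 1/m)] − 1.96):

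| m | Power |
|---|---|
| 20 | 99% |
| 15 | 98% |
| 10 | 94% |
| 5 | 77% |

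For m = 10 the standard error is 0.689, 2.40 / 0.689 = 3.48, and Φ(3.48 − 1.96) = Φ(1.52) = 0.94. If m = 0, site and group coincide and no analysis can separate them. A site term fitted to all the data would be estimated from controls only, and would rest on the untestable assumption that site acts alike in patients and controls.

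**The case against.** The strongest reply is that the article permits a site difference but does not establish one. This stands. The wording for controls is an either/or with no split, and if every control attends Noarlunga there is no site difference. A reader might infer that site and transport delay do differ by group. The documents do not support that: they give no distance, route, transport time or clock time for either hospital, so the existence, direction and effect of any difference in delay are conjecture.

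Four further points deserve weight.

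- **Handling is described alike for all blood.** Tube type, inversion, cooling and isolation are common to both groups, and the article lists standardised handling as a strength. Two draw points do not contradict that. A limit on draw-to-isolation time commonly sits in a laboratory manual, so its absence here is not an error. The cooling window does not supply such a limit, however, and the different site rule remains whatever the manual says.
- **The route to EC50 is not shown.** Cells are diluted to a fixed concentration, which removes a simple yield difference. A loss that only scales IL-1β release would move Top, not EC50. This weakens the case for the primary parameter. Top and Hillslope are, however, also compared in the primary painCELL analysis.
- **The test differs.** The article plans an F-test on fitted curve parameters. The percentages above come from a t-test and are not the planned analysis's error rate.
- **The site statements may simply be loose.** The bracketed wording can be read as naming both hospitals, so this is an ambiguity to clear up rather than a firm contradiction.

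**Conclusion.** The point holds in a conditional form. The plan lets collection site be confounded with group in a primary comparison, by a stated rule and without matching on site. The size cannot be computed from the article and may be zero. With half the controls at Flinders and an assumed shift of 0.25 to 1 SD, the false-positive rate in a simple two-sided t-test with 20 per group is about 7% to 29–35%, against 5% with no Flinders draws.

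Two stronger readings go too far. One is that the false-positive rate would approach 87%. That requires every control at Flinders and a full 1 SD shift, and nothing in the article supports either. The other is that the problem cannot be repaired in analysis. That is so only if no control is drawn at Noarlunga; otherwise a comparison within Noarlunga remains, with useful power at the plan's own effect size.

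The study is exploratory and the within-patient synovial comparison is unaffected. This is a cheap improvement to the design, not a flaw that invalidates it.

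**What to change.** 1. In Sample collection, have control blood drawn at Noarlunga by default, with the same handling and transport as patient blood.
2. Reconcile Aim, design and setting of the study with Sample collection, so that both name the same collection site or sites for each group.
3. Record collection site, draw time and isolation start time for every blood sample.
4. If a control has to be drawn at Flinders, flag the sample and repeat the blood comparison with Noarlunga controls only. With 10 such controls, power is about 94% at the plan's effect and SD (normal approximation).

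**Cost.** Some controls travel further, which may slow control recruitment slightly. Each sample needs a site entry and two time stamps. No extra participants or assays are needed. The article plans recruitment from March 2026 and states that no samples had been collected, so the change is easiest before the first draw.
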